**Methods:**

This protocol addresses the quantitative branch of a multicenter project (10 teams) for the creation of a cohort of at least 3,083 persons aged 35 to 74 years from 9 Autonomous Communities (AACC). The personal variables to evaluate are self-efficacy, activation, health literacy, resilience, locus of control, and personality traits. Socio-demographic covariates and social capital will be recorded. A physical examination, blood analysis, and cognitive evaluation will be carried out.

Several sets of six Cox models (one for each independent variable) will analyze the incidence of morbidity (objective 1); all-cause mortality and the rest of the dependent variables (objective 2). The models will be adjusted for the indicated covariates, and random effects will estimate Potential heterogeneity between AACC.

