The dependent variables in this study are morbidity, all-cause mortality, adoption of healthy lifestyles, quality of life, and utilization of health services. The information regarding the main dependent variables will be recorded at baseline and during the follow-ups at 5 and 10 years through surveys, physical examination and review of the medical records. The presence of morbidities will be assessed through the diagnoses in the medical records and physical examination. The medical records will also be the source to assess all-cause mortality.

Regarding the physical examination, blood pressure of participants will be measured and hypertension defined following the recommendations and criteria of the Spanish Hypertension Society. The ankle-brachial index (ABI) will be measured with a Vasera device (Fukuda Denshi), and peripheral arterial disease considered when ABI < 0.9. Weight and height will be measured to obtain the body mass index (BMI), and overweight and obesity will be considered if 25 ≤ BMI < 30 and BMI > 30, respectively. Waist circumference will also be measured. Blood testing will be performed to measure fasting glucose levels, glycated hemoglobin (HbA1c), total, low and high-density lipoprotein cholesterol, triglycerides, and creatinine.

For each participant, morbidity will be recorded at baseline and during follow-up by considering all the active conditions in the medical records at the time of the visit. We will define incident morbidity as the onset of any of the following 17 group conditions, provided they are not present at baseline: hypertension, ischemic heart disease (angina or acute myocardial infarction), heart failure, cardiac arrhythmias, diabetes mellitus, ischemic stroke, peripheral arterial disease, chronic obstructive pulmonary disease, asthma, any type of arthritis, osteoporosis, any type of cancer, Parkinson’s disease, one or more affective disorders (depression, anxiety), one or more psychotic disorders (schizophrenia, psychosis, bipolar disorder), dementia (including Alzheimer’s disease), and obesity. If we detect any frequent condition at follow-up that has not already been included in these 17 proposed groups, we will add a new group category.

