The evaluation of the participants’ mental health will also include the following: a questionnaire on the generalized anxiety disorder (GAD-7) (87), which evaluates the presence of symptoms; examination of the diagnostic criteria for major depression, using the PHQ-9 (88); and estimation of the risk of depression (89), in participants with no diagnosis of a major depressive episode.

We will evaluate the several lifestyles: adherence to the Mediterranean diet, assessed with the PREDIMED (82) and PREDIMED plus (83) questionnaires; type of diet, determined by asking the participants if they follow any specific diet (e.g., vegetarian, vegan); level of physical activity, assessed with the International Physical Activity Questionnaire (84); smoking habit, measured with the 4-question scale adapted from the WHO MONICA study (90); alcohol consumption, considering the total units during the past week and a question on the monthly frequency of excessive consumption (binge drinking) over the past year; and sleep, evaluated using the Pittsburgh Sleep Quality Index (85), the overall number of sleeping hours, usual bedtime, and waking-up time.

The quality of life will be determined using the EUROQol 5D-5L health questionnaire (86), and a question on self-perceived well-being. Finally, the utilization of health services for the last 12 months previous to inclusion into the study will be extracted from electronic health records. Where the research team may have no access to electronic health records, the utilization of health services will be assessed with a survey answered by the participants. The items will enquire on the number of visits (to the emergency department, primary care, and other specialties), hospital admissions, diagnostic tests, and pharmacological treatment (medication, dose, total daily dose, and duration).

Additionally, we will consider the following groups of covariates: sociodemographic, social, functional capacity, and stress level.

We will register the following sociodemographic variables: date of birth, sex, sex orientation, and gender identity (SOGI questions), marital status, nationality, and employment status. We will also consider occupational social class, defined with the educational level and occupation. Participants will answer questions on employment conditions (six items), domestic and care work (six items), income level and economic situation (four items), and housing and material situation.

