During the visit, participants will be invited to answer the questionnaires and the physical examination will be performed. The information collected in the self-administered questionnaires will be reviewed; if someone has not been able to fill them out, they will do it during the visit. On this first visit, a fasting blood sample extraction will be scheduled to determine (on a second visit) the parameters explained before. Finally, a letter with the examination results will be sent to each participant to allow consultation with the professionals from their health center if any abnormalities were detected. Figure 2 shows the data collection process with the actions that will affect the participants included in the study.

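### The protocol gives conflicting rules for which conditions are present at baseline, so disease first found by the study's own baseline examination or blood test could be scored as incident morbidity

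*Protocol article*

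**What the plan says.** The Variables section (2.4) of the Protocol article names the sources for morbidity three times, each time differently.

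- The main dependent variables, at baseline and at 5 and 10 years, are recorded "through surveys, physical examination and review of the medical records".
- On morbidity specifically: "The presence of morbidities will be assessed through the diagnoses in the medical records and physical examination".
- Each participant's morbidity, at baseline and during follow-up, is recorded "by considering all the active conditions in the medical records at the time of the visit".

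The outcome definition follows directly on the third statement: "We will define incident morbidity as the onset of any of the following 17 group conditions, provided they are not present at baseline".

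The same section gives cut-offs for peripheral arterial disease (ABI) and obesity (BMI) and refers to a national society's criteria for hypertension. Fasting glucose and HbA1c are measured, but no criterion turns them into diabetes. The PHQ-9 is used to examine criteria for major depression and the GAD-7 to assess anxiety symptoms. Table 1 lists both under dependent variables, but nothing ties either to the affective-disorder group.

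Under Data collection process (2.5), the fasting blood sample is booked at the first visit for a second one. After that, "a letter with the examination results will be sent to each participant to allow consultation with the professionals from their health center" if something abnormal was found.

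**The concern.** Incidence can be no better defined than the baseline status it starts from. The last of the three source statements stands next to the outcome definition, so a data manager would naturally implement it, and it leaves the examination out. A blood result that does not yet exist cannot be an active condition in the record at that visit. The study then tells participants their results and invites them to see their health centre. A condition that was there at entry may then reach the record weeks or months later and meet the definition of onset.

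Such events would cluster just after time zero in the Cox models. They also need not be balanced across the exposures. People with low health literacy may have more undiagnosed disease at entry, which would push the RR for low literacy up. Activated people may be more likely to act on the letter, which would push the RR for low activation down. The direction therefore cannot be presumed. The study looks for a small effect (RR 1.1 at 10 years), so a small distortion matters.

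**Working it through.** **1. The two morbidity-specific rules side by side.** Take a participant with a finding at the baseline assessment and no earlier diagnosis.

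| Baseline finding | Records plus examination | Records only, at the visit |
|---|---|---|
| Raised blood pressure, low ABI, obesity | Present | Not present, so at risk |
| Glucose or HbA1c suggesting diabetes | Unclear: depends on whether blood tests count as examination; no criterion stated | Not present; the result comes after the visit |
| Positive PHQ-9 or GAD-7 | Not covered, unless the general statement on surveys extends to morbidity | Not present |

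The rules disagree on the first row and leave the other two open or contrary. Whether blood tests belong to the examination is itself unsettled. They are described in the paragraph on the physical examination, but the abstract lists them apart: "A physical examination, blood analysis, and cognitive evaluation will be carried out".

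**2. The plan's own figure.** Inputs from Sample size (2.3): two-sided alpha 0.05, power 80%, 10-year incidence about 60%, RR 1.1, 30% loss, 1,793 exposed and 1,290 non-exposed (ratio 1.39). I take 60% as the non-exposed risk, which the article does not state, so the exposed risk is 0.60 × 1.1 = 0.66. The two-proportion formula with continuity correction gives 900 + 1,251 = 2,151 evaluable, and 2,151 / 0.7 = 3,073, against the stated 3,083. The figure reproduces closely and is not in dispute. It supplies the 60% and the 1.1 used below.

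**3. No true effect, misclassification differing by exposure.** Let *I* be the true cumulative incidence and *q* the fraction with undiagnosed baseline disease later scored as incident. Observed incidence = *q* + (1 − *q*) × *I*. The article gives no value for *q*, so every *q* here is an assumption.

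- 10 years, *q* = 15% (low literacy) vs 10%, all diagnosed after the letter: 0.15 + 0.85 × 0.60 = 0.66; 0.10 + 0.90 × 0.60 = 0.64; RR = 1.03.
- 10 years, *q* = 7.5% vs 5%: 0.63 / 0.62 = 1.016. Reversed: 0.62 / 0.63 = 0.984.
- 5 years, constant hazard: *I* = 1 − 0.4^0.5 = 0.3675. With 15% vs 10%: 0.15 + 0.85 × 0.3675 = 0.4624; 0.10 + 0.90 × 0.3675 = 0.4308; RR = 1.07, against the plan's 5-year target of 1.2.
- 10 years, 15% undiagnosed in both groups, but 60% of less activated and 90% of highly activated people diagnosed after the letter; the rest keep the 60% risk. Low activation: 0.15 × (0.6 + 0.4 × 0.6) + 0.85 × 0.6 = 0.636. High activation: 0.15 × (0.9 + 0.1 × 0.6) + 0.85 × 0.6 = 0.654. RR = 0.97, the opposite sign.

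**4. True RR 1.1, misclassification equal in both groups.** Evaluable: 1,793 × 0.7 = 1,255 and 1,290 × 0.7 = 903. Power is by the normal approximation without continuity correction.

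| *q* in both groups | Exposed | Non-exposed | RR | Power |
|---|---|---|---|---|
| 0 | 0.660 | 0.600 | 1.100 | 81.4% |
| 2% | 0.667 | 0.608 | 1.097 | 80.2% |
| 5% | 0.677 | 0.620 | 1.092 | 78.3% |
| 10% | 0.694 | 0.640 | 1.084 | 74.9% |

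**The case against.** A reader might infer that the blood tests, PHQ-9 and GAD-7 are excluded from baseline status. The article nowhere says so, and several features point the other way. Surveys are a named source for the main dependent variables. Blood testing sits in the physical-examination paragraph. Table 1 puts PHQ-9 and GAD-7 among the dependent variables, where morbidity is their natural home. Depression risk is estimated only in people without a diagnosed major depressive episode, which suggests that the PHQ-9 helps to settle baseline status. The outcome definition also speaks of conditions being present, not of their being recorded. All of this stands, and it rules out the stronger reading.

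Three further objections also have force. Under the records-plus-examination sentence, hypertension, peripheral arterial disease and obesity found at the visit are covered. The article does not say that the letter carries questionnaire scores, so the letter route cannot be asserted for depression or anxiety. And missing cut-offs for glucose, HbA1c, PHQ-9 or GAD-7 are detail that an article may leave to a fuller document; on their own they would be no finding.

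These objections do not remove the conflict. The records-only sentence is a stated rule, not an omission. It stands next to the outcome definition and differs from the two source statements before it. One can read the sentences as complementary, but the text does not require it, and the choice changes who is at risk.

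**Conclusion.** The point holds as a conflict in the definition of the primary outcome, with a real but unquantified risk of counting prevalent disease as incident. It bites if the records-only sentence is followed. It then reaches hypertension, peripheral arterial disease, obesity and diabetes through the examination and blood test. Under either morbidity rule, diabetes and affective disorder are the least settled.

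The size rests on fractions that are not in the article. Under the assumptions shown, the spurious 10-year RR lies between about 0.97 and 1.03, at most about a third of the excess the study is sized to detect. Equal misclassification of 5% to 10% would lower power from 81.4% to between 78.3% and 74.9%. A reader might conclude that the design will create or reverse an association. The documents do not support that: it would take differential fractions that nobody has yet observed. This should be fixed before follow-up data are analysed, because a rule chosen afterwards would be post hoc for the primary outcome.

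**What to change.** Reconcile the source statements in Variables with Data collection process, and state one rule that applies identically at baseline, 5 and 10 years:

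- A condition is present if it is a record diagnosis, or if it meets a pre-named criterion on the study's own examination or blood test (hypertension, peripheral arterial disease, obesity, diabetes). Bring the records-only sentence into line with this.
- A diagnosis that results from the baseline examination or the results letter is classified as prevalent.
- A sensitivity analysis starts risk time 12 months after baseline.
- State in advance whether positive PHQ-9 or GAD-7 results count as prevalent affective disorder. Treating a positive screen as a disorder is debatable, so a sensitivity analysis that removes baseline screen-positives from risk for that group is a reasonable choice.

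The cost is mainly wording, since all the measurements are already planned. The downside is somewhat fewer at-risk participants and events for the affected conditions, by an amount that the baseline data will show. A participant prevalent for one group stays at risk for the others.

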**Figure 1 fig1:**
[figure not shown]
Diagram showing the causal relationship proposed in the study between the independent variables (personal aptitudes), the dependent variables (morbidity, lifestyles, quality of life, use of services and mortality) and the modulating effect of the covariates.

This is a multicenter study for the creation of a prospective cohort of persons assigned to Primary Healthcare (PHC) centers within nine autonomous communities (AACC; Catalonia, the Basque Country, Castilla y León, Aragón, Galicia, the Balearic Islands, Castilla La Mancha, Andalusia and Madrid). Follow-up examinations and evaluations will be at 5 and 10 years from the entry date.

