### Statistical analysis

2.6.

The statistical analysis will include a descriptive analysis. Percentages of the categorical variables will be calculated for each AACC. Continuous variables with a normal distribution will be described with the mean (standard deviation, SD); otherwise, the median (first and third quartile) will be used. The analyses will be stratified by sex. Bivariate analyses will be performed using the *t*-test for independent samples, or the Mann–Whitney test when required, to analyze continuous variables; and the Chi-squared test for proportions.

Objective one will analyze the incidence of morbidity, defined as the onset of any new condition out of the 17 considered. To this end, a Cox model will be built for each independent variable, and adjusted for the above-mentioned covariates. Potential heterogeneity between AACC will be estimated by introducing random effects in the model. Sensitivity analyses will examine loss to follow-up rates. Objective two will analyze the incidence of the rest of the dependent variables (except incidence of morbidity) using also Cox models, one for each of the six independent variables, adjusted for the covariates. We will calculate the incidence of all-cause mortality and its Kaplan–Meier, stratified by the categorical variables and AACC. Potential heterogeneity will be estimated, and sensitivity analyses performed as in objective one.

Before obtaining the follow-up information at 5 and 10 years, we will describe and analyze the gathered data at baseline. To this end, general linear multilevel models will be used to examine the association of the dependent variables (lifestyles, quality of life, and use of services), with the six independent variables, adjusted for the registered covariates (age, sex, occupational social class, social capital, functional capacity, and stress level). Potential disparities between AACC will be captured by including random effects in the models.

Statistical significance will be considered at *p*-values < 0.05. The analyses will be carried out using the Statistical Package for the Social Sciences (SPSS) version 26.0, and the R-software.

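### Morbidity is read from conditions active at the 5- and 10-year visits, which does not match the onset endpoint or the Cox model built on it

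*Protocol article*

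**What the plan says.** Section 2.4 (Variables) gives the recording rule, which applies at entry and at later visits alike. Morbidity is established "by considering all the active conditions in the medical records at the time of the visit". The next sentence gives the endpoint: "We will define incident morbidity as the onset of any of the following 17 group conditions, provided they are not present at baseline". The same section names the sources and times. Information on the outcomes "will be recorded at baseline and during the follow-ups at 5 and 10 years through surveys, physical examination and review of the medical records". On diagnoses, the section states: "The presence of morbidities will be assessed through the diagnoses in the medical records and physical examination". For death it adds: "The medical records will also be the source to assess all-cause mortality".

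Section 2.1 fixes the schedule: "Follow-up examinations and evaluations will be at 5 and 10 years from the entry date". Section 2.6 (Statistical analysis) again describes the objective-one outcome as the onset of a new condition among the 17, and continues: "To this end, a Cox model will be built for each independent variable". The only sensitivity analysis named for this objective concerns loss to follow-up.

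**The concern.** A list of conditions active on a given day is a point-prevalence measure. The endpoint is a first onset, and a Cox model needs a time for it. Four consequences follow if the recording rule is applied as worded:

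- **Resolved conditions.** An affective disorder or a treated cancer that begins and is closed between two visits is not active at either.
- **Recurrences.** Baseline status is read by the same rule. A past condition that is inactive at entry therefore counts as absent, and its return counts as onset.
- **No visit.** Someone who dies or does not attend has no visit at which active conditions are read.
- **Onset time.** Hypertension, obesity and peripheral arterial disease first found by examination are known only to have begun in the preceding five years.

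This is the primary endpoint and enters all six objective-one models. The sample size targets RR 1.1 with little spare power, so modest misclassification matters.

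**Working it through.** **Inputs from section 2.3 (Sample size).** Two-sided alpha 0.05, power 0.80, about 60% incidence over roughly 10 years, RR 1.1, 30% loss, 1,793 exposed and 1,290 non-exposed (ratio 1.39).

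**Reproducing the planned figure.** Take 60% as the non-exposed risk, so the exposed risk is 0.60 × 1.1 = 66%. The two-proportion formula with continuity correction gives 900 non-exposed and 2,151 in total; 2,151 / 0.70 = 3,073, against the stated 3,083. The log-RR formula with binomial variance gives 3,060. The figure reproduces on this reading.

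**Planned power.** Evaluable numbers are 0.70 × 1,290 = 903 and 0.70 × 1,793 = 1,255. Power = Φ[(d − 1.96·SE0)/SE1], with SE0 the pooled and SE1 the unpooled standard error. Here d = 0.06, SE0 = 0.0210 and SE1 = 0.0211, so power = Φ(0.89) = 81%.

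**Effect of misclassification.** The documents give no rates, so each row is an assumption. Missed cases multiply the risk by (1 − share missed). False onsets add their share of the true non-cases.

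| Assumption | Non-exposed | Exposed | RR | Power |
|---|---|---|---|---|
| None | 60.0% | 66.0% | 1.100 | 81% |
| 5% of cases missed in both groups | 57.0% | 62.7% | 1.100 | 76% |
| 10% missed in both | 54.0% | 59.4% | 1.100 | 71% |
| 5% vs 7% missed | 57.0% | 61.4% | 1.077 | 53% |
| 5% vs 10% missed | 57.0% | 59.4% | 1.042 | 20% |
| 5% of non-cases scored as onset | 62.0% | 67.7% | 1.092 | 78% |
| 10% of non-cases scored as onset | 64.0% | 69.4% | 1.084 | 75% |

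Missing 5% or 10% equally raises the required total from 3,073 to 3,503 or 3,981.

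**Effect of ties, if visit dates were the event times.** With constant hazards the true HR is ln(0.34)/ln(0.40) = 1.0788/0.9163 = 1.177. Five-year event-free shares are √0.40 = 63.2% and √0.34 = 58.3%. Expected events are then 332 + 523 at year 5 and 210 + 305 at year 10, so about 1,370 events fall on two times. Maximising the Cox partial likelihood on these counts gives:

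- Breslow ties: HR 1.134, a loss of 1 − ln(1.134)/ln(1.177) ≈ 23% of the log HR.
- Efron ties: HR 1.174, a loss of about 2%.

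**The case against.** The strongest defence is that the sentence on active conditions only describes recording. The definition that follows it says onset, section 2.6 repeats this, and record review could supply diagnosis dates and cover people who have died. A condensed article may leave date extraction, ties and censoring to a fuller document. This stands in part: the consequences for deaths and onset times are inferred from the rule, not stated. It does not remove the point, because the one sentence that says how the records are read limits them to active conditions at the visit. That is a stated rule in conflict with the stated endpoint, not a missing detail.

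It is also fair that many of the 17 groups are usually lasting, and that one missed episode matters only if the person has no other new condition recorded. This limits the size of the problem.

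Two stronger readings are tempting and not supported:

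- **That deaths shrink the contrast.** Suppose 4% of non-exposed and 5% of exposed people die before the visit, 90% of them with a new condition. Keeping them as event-free gives 0.60 − 0.036 = 56.4% and 0.66 − 0.045 = 61.5%, so RR 1.09 and power 66%. But nothing in the article codes them this way. Removing them gives 0.564/0.96 = 58.75% and 0.615/0.95 = 64.7%, so RR 1.10, with power 81% if these deaths fall within the planned 30% loss. The attenuation comes from the coding.
- **That ties cost about a quarter of the effect.** This needs both visit dates as event times and Breslow handling. The article fixes neither.

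**Conclusion.** The point holds as a conflict between the recording rule on one side and the endpoint definition and Cox model on the other. The missed resolved conditions, the recurrences scored as onset and the interval-only knowledge of examination findings follow directly from the rule as worded. The dependence on a visit follows too, but how people who died would be classified is not stated.

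The size cannot be computed from the documents. Under the assumptions shown, equal 5% under-capture leaves RR at 1.1 and lowers power from about 81% to about 76%. A small imbalance, 5% against 7%, lowers RR to 1.077 and power to about 53%. These figures rest on reading 60% as the non-exposed risk and on 70% retention. Tie bias is secondary and is negligible under Efron. Severity: should be fixed, with moderate confidence.

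**What to change.** Where records are accessible:

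1. Replace the active-at-visit rule with dated diagnosis entries for the 17 groups, open or closed, over the whole record.
2. Use lifetime history before inclusion to decide who is at risk for each condition, and settle this before follow-up outcomes are seen.
3. Take as the event the first dated entry from inclusion to death, transfer out or 10 years, including for people who died or did not attend. Censor those without an event at death or at the end of record coverage.
4. Treat conditions detected only by examination as interval-censored between visits, for example with a discrete-time complementary log-log model, which still yields a hazard ratio.

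The cost is a changed extraction query on records already under review, one model specification and a little more programming. No extra visits are needed, and the sample size does not change through the fix itself.

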### Study objectives and hypotheses

1.1.

This project was designed as a hybrid study, composed of a quantitative part (exposed in this article) and a qualitative part (published in another article).

The quantitative part of the DESVELA cohort has the following objectives:

To analyze whether personal aptitudes related to certain behaviors (self-efficacy, activation, health literacy, resilience, locus of control, and personality traits) are independently associated with the incidence of morbidity.To analyze whether personal aptitudes related to certain behaviors (self-efficacy, activation, health literacy, resilience, locus of control, and personality traits) are independently associated with lower all-cause mortality, improved engagement in healthy lifestyles, higher quality of life, and lower utilization of the health services during follow-up.

We hypothesize that personal aptitudes that are related to positive behaviors (a higher self-efficacy, activation, health literacy, resilience, an internal locus of control, and positive personality traits) will be independently associated with a lower incidence of morbidity. We also hypothesize that personal determinants related to positive behaviors (a higher self-efficacy, activation, health literacy, and resilience, an internal locus of control, and positive personality traits) will be independently associated with all-cause mortality, engagement in healthy lifestyles, higher quality of life, and more optimal use of the health services during follow-up.

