### Participants

2.2.

We will include persons aged 35–74 years assigned to the above-mentioned PHC centers, selected by random sampling. Exclusion criteria will apply to persons with a terminal condition or institutionalized at the time of recruitment; persons with intellectual disabilities, dementia, or language difficulties; and persons who plan to move out of Spain within 5 years from study initiation.

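### The covariates fixed for the objective 1 Cox models leave out baseline morbidity, so an independent association with new morbidity could be confounded by existing illness, to an unknown size and sign.

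*Protocol article*

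**What the plan says.** Objective 1 (Study objectives and hypotheses) asks whether six personal aptitudes "are independently associated with the incidence of morbidity".

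The adjustment set is stated in Variables: "we will consider the following groups of covariates: sociodemographic, social, functional capacity, and stress level". The paragraphs that follow itemise each group, and no chronic condition or condition count appears. The covariables block of Table 1 has none either. Statistical analysis then applies the set to objective 1: "a Cox model will be built for each independent variable, and adjusted for the above-mentioned covariates". For the separate cross-sectional models at baseline, the same section gives a shorter list, again without morbidity: "adjusted for the registered covariates (age, sex, occupational social class, social capital, functional capacity, and stress level".

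Morbidity appears only as a dependent variable. It is nevertheless collected at entry ("morbidity will be recorded at baseline and during follow-up by considering all the active conditions in the medical records"), and the event is defined relative to it: "onset of any of the following 17 group conditions, provided they are not present at baseline". Prevalent chronic disease will be common in the cohort, because eligibility is broad ("We will include persons aged 35–74 years assigned to the above-mentioned PHC centers, selected by random sampling") and the exclusions concern terminal illness, institutionalisation, intellectual disability, dementia, language difficulties and planned emigration.

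**The concern.** A participant with none of the 17 groups at entry can have any of 17 first events. A participant with several has fewer left, but may have a higher hazard for each of those. The objective 1 model puts both in one risk set and does not adjust, stratify or restrict on the difference.

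The omission matters only if baseline disease is also related to the aptitudes. The Introduction gives reason to expect this. It links personality traits, external locus of control, low activation and low health literacy to worse health or disease. It links self-efficacy and resilience to mental health or cognition, and affective disorders are one of the 17 groups. The aptitudes are measured at the same baseline at which illness may already be present, so illness could shape the scores as well as the reverse.

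What is at stake is the word independent in the objective. A study sized for a 10-year risk ratio of 1.1 has little room for confounding of even a few per cent.

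**Working it through.** **1. What effect the study is sized for.** Inputs from Sample size: two-sided alpha 0.05, power 0.80, incidence about 60%, risk ratio 1.1, loss 30%, groups of 1,793 and 1,290 (ratio 1.39). Reading 60% as the risk in the non-exposed gives 0.60 versus 0.66. A two-proportion calculation with continuity correction then needs 2,151 evaluable participants, and 2,151 / 0.70 = 3,073, against the stated 3,083. With 60% as the exposed risk the same method gives 3,892, and with 60% overall 3,551. The design contrast is therefore 60% versus 66%.

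**2. That contrast as a hazard ratio.** Under proportional hazards, HR = ln(1 − 0.66) / ln(1 − 0.60) = ln 0.34 / ln 0.40 = 1.0788 / 0.9163 = 1.18, with log HR 0.163. The design's 1.1 is a risk ratio and must not be set directly beside a hazard ratio.

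**3. Spurious hazard ratio when the true aptitude effect is null.** Assumed inputs, not in the documents: the exposed group enters with d = 0.3 to 0.5 more conditions on average, and each condition multiplies the hazard of a new one by h = 1.15 to 1.30. To first order the unadjusted HR is h^d. The implied risk in the exposed is 1 − 0.40^HR, and the risk ratio divides this by 0.60.

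| d | h | HR = h^d | Risk in exposed | 10-year RR | ln HR / 0.163 |
|---|---|---|---|---|---|
| 0.3 | 1.15 | 1.043 | 0.615 | 1.03 | 0.26 |
| 0.5 | 1.15 | 1.072 | 0.626 | 1.04 | 0.43 |
| 0.3 | 1.30 | 1.082 | 0.629 | 1.05 | 0.48 |
| 0.5 | 1.30 | 1.140 | 0.648 | 1.08 | 0.80 |

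The bias is about a quarter to four-fifths of the design effect on the log-hazard scale.

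**4. Cross-check by a different method.** This takes the large-sample limit of a Cox model that omits a binary indicator of baseline disease. Assumed: prevalence 30% in the non-exposed and 35% to 50% in the exposed; true aptitude HR 1.00. From the protocol: 10-year incidence 60%, exposure 58.3%, and 3,083 × 0.70 × 0.60 = 1,295 events. The standard error of the log HR is 1 / √(1,295 × 0.583 × 0.417) = 0.056.

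- If baseline disease raises the hazard (HR 1.3 to 2.0), the fitted aptitude HR is 1.01 to 1.15, the 10-year RR is 1.01 to 1.09, and the chance of p < 0.05 is 6% to 69%.
- If depletion of the remaining conditions dominates (HR 0.8 for baseline disease), the fitted HR is 0.96 to 0.99 and the chance of p < 0.05 is 5% to 12%.
- With the indicator in the model, the fitted HR is 1.00 and the chance is 5%.

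Neither calculation allows for the covariates already in the model, so both show the bias before any proxy adjustment.

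**The case against.** **Partial proxies.** Age and WHODAS functional capacity are in the model and carry part of the disease burden. This stands, and it makes the residual bias smaller than the figures above by an amount the documents do not allow one to estimate. It does not remove the concern, because hypertension, obesity or diabetes can be present without measurable disability.

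**Mediation.** Disease at entry may partly result from long-standing aptitudes, personality traits above all, so adjusting for it could remove part of the effect of interest. This also stands, and it is why both models should be shown. It does not justify leaving the variable out altogether: the plan already adjusts for functional capacity, which existing disease can affect, so it does not protect a total effect as it is.

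**Prevalent disease is already handled.** A condition counts only "provided they are not present at baseline". That prevents misclassification of old disease as new. It does not equalise the hazard between people with and without existing conditions.

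**A condensed article.** A full analysis plan may say more. But the article does not leave the set open: it lists the groups, itemises them and refers the Cox models back to them. The shorter list in Statistical analysis is weak corroboration only, since it belongs to the cross-sectional models.

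**Stronger readings to avoid.** A reader might infer that the bias is as large as the effect the study is sized for. That sets a hazard ratio beside a risk ratio; on a common scale the assumed range stays below the design effect. A reader might also infer that the bias must inflate the association, or that reverse causation is established. The documents support neither. Depletion works in the opposite direction, and the Introduction reports associations that, where they imply a direction, mostly run from aptitude to health. Nor do the documents show that an independent association could not be supported, only that it would be open to this alternative explanation.

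**Conclusion.** The point holds as an omission from a stated adjustment set. Baseline morbidity is collected, helps define the outcome and is a plausible confounder, yet the objective 1 models as written do not use it. An association reported as independent would remain open to confounding by existing illness.

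Size and sign are not known from the documents. Under the assumed differences in condition count and hazard multipliers, a null aptitude would show a 10-year risk ratio of about 1.03 to 1.08. The cross-check spans 1.01 to 1.09 when existing disease raises the hazard, with a fitted hazard ratio as low as 0.96 when depletion dominates. All of these figures rest on assumed inputs and are before proxy adjustment. They show that the bias could be material for this design, not that it will be.

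**What to change.** - Add the baseline count of the 17 groups (0, 1, 2, 3 or more) to the objective 1 Cox models, as a covariate or as a stratum. Add it as a covariate to the mortality and service-use models.
- Report each of these results with and without the term, and say in advance that the two answer different questions because baseline disease may be partly a mediator.
- Add a sensitivity analysis restricted to participants with none of the 17 groups at entry. There the event set is the same for everyone.

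Cost: no new data, no change to the sample size of 3,083, and a little more analysis and reporting. The main downside is possible over-adjustment for a mediator, which showing both models makes visible. The restricted analysis will be less precise, by an amount that depends on how many participants enter free of all 17 groups, which the documents do not state.
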